#### Secondary Outcome Measure

We will estimate the proportion of cases with at least 1 level of improvement in mRS grade and the 95% CI by using the scoring method at 180 (±14) days after MSC infusion. We will also estimate the mean changes in FMA, National Institutes of Health Stroke Scale, and Functional Independence Measure scores from immediately before (−14 to 0 days) MSC infusion to 180 (±14) days after MSC infusion and the 95% CIs by using the Wald method.

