**Methods:**

The (phase 2) trial will be a single-arm, open-label trial with the primary objective of confirming the safety and efficacy of autoserum-expanded autologous MSCs (STR-01; produced under good manufacturing practices) when administered to patients with chronic brain injury. The estimated number of enrolled participants is 6 to 20 patients with a modified Rankin Scale grade of 3 to 5. The assessment of safety and the proportion of cases in which the modified Rankin Scale grade improves by 1 point or more at 180 days after the injection of STR-01 will be performed after MSC infusion.

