### Sample Size

We will recruit 10 people (minimum: 6; maximum: 20) with a modified Rankin Scale (mRS) grade of 3 to 5. The focus of our trial is to establish safety and potential efficacy. However, it should be noted that if the proportion of cases in which the mRS grade improves by 1 point or more exceeds 10%, the trial will provide significant clinical benefit. To detect a difference by using a *Z*-test with continuity correction, a minimum of 6 people is required. Thus, the target sample size of people with an mRS grade of 3 to 5 was determined to be 10 (minimum: 6; maximum: 10), under the consideration of dropout.

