#### Primary Outcome Measure

The valid target population is patients with an mRS grade of 3 to 5 before MSC infusion. We assume that the proportion of cases without MSC infusion in which the mRS grade improves by 1 point or more will be 0.1%. We will perform a Z-test with continuity correction at 180 (±14) days after MSC infusion.

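### Wald 95% intervals for the mean FMA, NIHSS and FIM changes are too short at the planned sample size: about 89% coverage at 6 patients, 92% at 10 and 93.5% at 20

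*Protocol article*

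**What the plan says.** Under Statistical Analysis, Secondary Outcome Measure, the protocol article states: "We will also estimate the mean changes in FMA, National Institutes of Health Stroke Scale, and Functional Independence Measure scores", from just before infusion to day 180, with "the 95% CIs by using the Wald method". The same paragraph assigns a different method, the score method, to the interval for the proportion of patients whose mRS grade improves. It gives no formula, quantile or degrees of freedom for the Wald intervals and mentions no small-sample correction. The opening of Statistical Analysis refers to a statistical analysis plan for details; that plan is not at hand.

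The number of patients is stated in three places:
- Abstract, Methods: "The estimated number of enrolled participants is 6 to 20 patients".
- Sample Size, first statement: "We will recruit 10 people (minimum: 6; maximum: 20".
- Sample Size, last sentence: the target "was determined to be 10 (minimum: 6; maximum: 10), under the consideration of dropout".

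The target is therefore 10 and the minimum 6. The maximum is 20 in two places and 10 in the third.

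**The concern.** A Wald interval for a mean multiplies the estimated standard error by the normal quantile 1.96. That is justified when the SD is known or well estimated. With 6 to 20 patients the SD is itself uncertain, and the multiplier that allows for this is the Student t quantile on n − 1 degrees of freedom. Using 1.96 makes every interval too short by a fixed factor, whatever the scale.

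At stake is how precise the continuous efficacy results appear. The trial has no control arm, so a reader will naturally ask whether the interval for the mean change excludes zero. The Discussion says that the data will feed into the protocol of a larger trial, so overstated precision could carry forward. The Secondary Outcomes section defines differences for item scores as well as totals; if item-level intervals are reported, each would use the same short multiplier.

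**Working it through.** **Inputs**
- Interval: mean change ± 1.96 × SD/√n, the usual meaning of Wald (Secondary Outcome Measure; the formula itself is not written there).
- Nominal level: 95%, two-sided (same section).
- n = 6, 10 and 20: minimum, target and the larger stated maximum (Sample Size; abstract).
- Assumption: within-patient changes are roughly normal. No SD is needed, because it cancels.

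**Step 1: coverage of the planned interval.** For normal changes, (mean − true mean)/(SD/√n) follows a t distribution with n − 1 degrees of freedom. Coverage is therefore 2 × F(1.96; n − 1) − 1, where F is the t distribution function.

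**Step 2: chance of wrongly excluding zero.** When the true mean change is zero, this is 1 − coverage for both directions together. By symmetry, half of it lies in the direction of improvement.
- n = 6: 1 − 0.8927 = 0.1073; half is 0.054.
- n = 10: 1 − 0.9184 = 0.0816; half is 0.041.
- n = 20: 1 − 0.9352 = 0.0648; half is 0.032.

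**Step 3: width of the t interval relative to Wald.** The ratio is t(n − 1, 0.975)/1.960.
- n = 6: 2.571/1.960 = 1.312.
- n = 10: 2.262/1.960 = 1.154.
- n = 20: 2.093/1.960 = 1.068.

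| | n = 6 | n = 10 | n = 20 | nominal |
|---|---|---|---|---|
| Wald coverage | 89.3% | 91.8% | 93.5% | 95% |
| Zero wrongly excluded, either direction | 10.7% | 8.2% | 6.5% | 5% |
| Zero wrongly excluded, towards improvement | 5.4% | 4.1% | 3.2% | 2.5% |
| t interval wider than Wald by | 31% | 15% | 7% | |

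The stated 95% is thus not reached at any planned n. Simulation with 200,000 normal samples per n agrees: Wald coverage was 89.3%, 91.9% and 93.6%, and t interval coverage was 95.0% at all three sizes.

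**Step 4: sensitivity to skewness.** With changes of exponential shape (an assumption, for illustration), simulated coverage is:

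| | n = 6 | n = 10 | n = 20 |
|---|---|---|---|
| Wald | 83.1% | 86.9% | 90.5% |
| t | 88.7% | 90.0% | 91.9% |

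Skewness makes the Wald shortfall worse. The t interval recovers part of it, not all.

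**The case against.** The strongest objection is that the article describes the analysis only briefly. Wald is sometimes used loosely for any estimate ± multiplier × SE, and the analysis plan or the software may in fact use a t quantile. If so, the numerical problem disappears and only the wording needs correcting. This lowers certainty about what will be computed. It does not remove the point, because the method is named rather than left open, and in its usual sense it is the normal-quantile interval.

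Four stronger readings are tempting, and the documents do not support them:
- *That these intervals are all the secondary efficacy evidence.* The same paragraph also plans the mRS improvement proportion with a score interval, which is unaffected.
- *That improvement will be falsely claimed 10.7% of the time at n = 6, against 5%.* That rate counts both directions. Towards improvement it is about 5.4% against 2.5%; the doubling stands, the absolute figures do not.
- *That a trial conclusion turns on these intervals.* The plan is to estimate mean changes. No test or success criterion is attached to FMA, NIHSS or FIM.
- *That n lies only between 6 and 10.* The abstract and the first Sample Size statement allow 20, where the shortfall is 1.5 percentage points (95 − 93.5).

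It is also fair to say that the t interval is exact only for normal changes, as Step 4 shows.

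**Conclusion.** The point holds as a limited one. Followed as written, the plan gives intervals for three continuous secondary scales that are too short: coverage is 5.7 points below nominal at the minimum n = 6 (95 − 89.3), 3.2 at the target of 10 (95 − 91.8) and 1.5 at 20. The conclusion rests on two assumptions: that Wald carries its usual meaning, and that the changes are roughly normal. If they are skewed, the shortfall is larger. The primary Z-test, the score interval for the mRS proportion and any decision in the trial are untouched. It is worth correcting because the error is systematic, runs towards overstated precision and is easily removed.

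**What to change.** In Secondary Outcome Measure, and in the analysis plan if it uses the same wording, replace the Wald method for the FMA, NIHSS and FIM changes with the paired t interval: mean change ± t(n − 1, 0.975) × SD/√n, where n is the number of patients with both measurements. If a t quantile is already intended, the same edit makes the text match the analysis.

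The edit is one phrase; visits, data collection and sample size do not change. The cost is wider intervals, by about 31%, 15% and 7% at n = 6, 10 and 20. Coverage may still fall below 95% with strongly skewed changes, so it helps to show the individual changes beside the intervals. Separately, the two maxima in Sample Size (20 and 10) should be reconciled, since the size of the shortfall depends on n.

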### Provisions for Posttrial Care

The participants of the trial will follow standard clinical procedures during the study; thus, there will be no specific posttrial care. As the participants are the patients within Japan’s National Health Insurance system, postcare will be provided through the National Health Insurance schemes, if necessary. Clinical research insurance for studies will also be covered.

### Access to Data

All investigators will have access to the trial data.

### Data Management

All participant trial data will be entered into the electronic data capture system hosted at the Translational Research Center for Medical Innovation (Kobe, Japan). The data collected will be deidentified by using unique study code numbers. To maintain the privacy of the participants, any reports of individual data will only consist of clinical data without any names, addresses, or identifying information. This complies with the university’s IRB guidelines. All patient-related information and data that are generated will be maintained on a secure server. Data monitoring will comply with the university’s policies, its guidelines, and the data management plan that was approved for the study. Data will be audited at an appropriate period by the EPS Corporation (Tokyo, Japan). At the completion of the study, the results will be submitted for publication in a peer-reviewed journal and presented at national and international conferences.

## Results

We received approval for our clinical trial from the Japanese PMDA on December 12, 2017. The trial will be completed on June 11, 2023. The registration term is 5 years. The recruitment of the patients for this trial started on April 20, 2018, at Sapporo Medical University Hospital in Japan.

## Discussion

The specific objective of our trial is to evaluate the safety and potential therapeutic efficacy of the intravenous infusion of autoserum-expanded autologous MSCs for patients with chronic brain injury. The patients who enrolled in our study with chronic brain injury and decreased neural function due mainly to brain trauma will receive an intravenous infusion of autologous MSCs that are expanded in autosera. A brain injury presents serious health and socioeconomic burdens that the development of an effective therapy could alleviate.

Various treatments have been developed that focus mainly on the acute phase, including neurorestorative, anti-inflammatory, and neuroprotective agents. However, no established medical therapies that promote effective therapeutic efficacy have been made, especially for the chronic phase. Therefore, a novel therapy that promotes recovery from brain damage after a chronic brain injury should be developed [29].

We previously reported on the safety, feasibility, and potential therapeutic efficacy of the intravenous infusion of autoserum-expanded autologous MSCs for patients with cerebral infarction [27] and subacute SCI [28]. The intravenous infusion of MSCs derived from bone marrow improves functional outcomes in experimental animal models of stroke [4-7,9-11], SCI [13,14,16,24,30,31], neonatal hypoxic ischemia [12], chronic epilepsy [17], cerebral small vessel disease [8,32], amyotrophic lateral sclerosis [33,34], and peripheral nerve injury [18,21]. Although the mechanisms underlying these beneficial effects have not been fully elucidated, potential mechanisms include neuroprotection and immunomodulation [14], the induction of axonal sprouting [13], remyelination [13], the restoration of the blood-brain and blood–spinal cord barriers [13,24], and the enhancement of remote gene expression responses [15].

We reported that infused MSCs facilitate neural plasticity in experimental models of neonatal [12] and adult [4,5] cerebral ischemia. Since brain injuries in the chronic phase are heterogenous injuries that are underpinned by numerous complex and interrelated pathophysiological conditions [35], it is conceivable that the enhanced neural plasticity resulting from MSC injection promotes structural rewiring, which might contribute to functional improvement in chronic state of neural diseases. In addition, there are other multimodal and orchestrated mechanisms, as shown in previous studies [3-13,15-18,25,28,32-34,36-38]. Given these considerations of the potential therapeutic effects of MSCs in a number of neurological disorders, we planned a clinical trial for chronic brain injury.

The purpose of our study is to address the safety and potential therapeutic efficacy of the intravenous infusion of autologous MSCs based on the primary outcome measures. If the intravenous infusion of autologous MSCs shows possible therapeutic efficacy and is shown to be safe without any major adverse effects, this approach could be successfully translated to a larger controlled and blinded clinical study in the future. The data from our study will be used to develop a new clinical protocol for any future, larger, definitive evaluation trials.

In conclusion, due to the promising therapeutic effects of autoserum-expanded autologous MSCs for stroke [27] and SCI [28], this approach should be evaluated for chronic brain injury, which shares many of the histopathological conditions that have been seen in patients with stroke and SCI. We thus believe that this cell therapy approach for patients chronic brain injury could have a significant impact and warrants evaluation in the near future [39].

## Abbreviations

3D-CTA: 3D computed tomography angiography
FMA: Fugl-Meyer assessment
IRB: institutional review board
MRI: magnetic resonance imaging
mRS: modified Rankin Scale
MSC: mesenchymal stem cell
PMDA: Pharmaceuticals and Medical Devices Agency
SCI: spinal cord injury
